### Data Management

2.13

After each assessment, assessors verify the data daily to ensure accuracy. The final study data set will be accessible only to the study manager, principal investigators, and data auditors. Upon completion of the study, all authors will have equal access to anonymized data. The principal investigator will securely store all hard and electronic copies of the collected data, ensuring that no access is granted to identifiable participant information. Manual data entries will undergo double‐checking to minimize errors. Online data will be carefully stored on a password‐protected server managed by the postgraduate program in Physiotherapy and Rehabilitation. Each participant is assigned a unique identification number, and data will be encoded securely using this ID. The ID number will be encrypted separately from any identifying information to maintain participant confidentiality throughout the study.

### Data Monitoring

2.14

Two independent individuals were appointed to monitor and audit group enrollment, the intervention protocol, and any adverse effects experienced by participants. They are not directly included in this study. These monitors have access to review data and conduct interim analyses. Any changes to the research or treatment protocol are promptly communicated by the principal investigator to the Ethical Review Board.

### Data Analysis

2.15

Data analysis will be performed by an independent statistician using SPSS version 22, with anonymized and encrypted data to ensure confidentiality. Prior to analysis, data will be screened for completeness and outliers. The parametricity of the data will be assessed using the Kolmogorov–Smirnov and Shapiro–Wilk tests, supported by evaluation of skewness and kurtosis and visual inspection of data distribution through histograms and normal probability plots. Descriptive statistics, including mean and standard deviation for normally distributed variables, median and interquartile range for non‐normally distributed variables, and frequency and percentage for categorical variables, will be used to summarize continuous and categorical data. Baseline characteristics, including body mass index and duration of diabetes, will be reported to assess group comparability, and exploratory subgroup analyses for high‐risk participants will be considered if clinically relevant patterns are observed. For comparisons across three time points (baseline, postintervention, and follow‐up), repeated‐measures ANOVA will be applied for normally distributed data, with the Friedman test used as the nonparametric alternative. Between‐group and within‐group differences will be analyzed using independent and paired *t*‐tests for parametric data, or Mann–Whitney *U* and Wilcoxon signed‐rank tests for nonparametric data, as appropriate. The laterality of PHP (unilateral or bilateral) will be recorded and incorporated into the analysis to minimize potential confounding effects on ROM and muscle strength outcomes. Effect estimates and mean differences will be reported with 95% confidence intervals alongside *p* values. All statistical tests will be two‐tailed, with statistical significance set at *p* < 0.05, *p* < 0.01, and *p* < 0.001. In addition, baseline, posttest, and follow‐up change scores will be evaluated, and an intention‐to‐treat analysis using the last observation carried forward method will be applied to handle missing data and preserve the validity of the analysis.

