In physiotherapy practice, various interventions have been reported, including electrical modalities such as iontophoresis with dexamethasone 0.4% or acetic acid 5%, which give pain relief and improve function within 2–4 weeks. Manual therapy techniques such as nerve mobilization (effective within 1–3 months), soft tissue mobilization, passive neural mobilization, gliding of the ankle joint posteriorly, the subtalar joint laterally, and the first tarsometatarsal joint anterior‐posteriorly, and distraction manipulation of the subtalar joint are also commonly used to reduce pain and restore mobility for people with PHP [13]. Other conservative approaches include taping, orthotic devices, and night splints. Calcaneal taping may provide pain relief temporarily within 7–10 days. Orthotic devices, such as specially designed foot orthoses, reduce pain and improve function over a short‐term period of approximately 3 months. Night splints, available in sock‐type, anterior, or posterior designs, are recommended for individuals with PHP lasting 6 months or more. They are typically worn for 1–3 months [15].

Studies on PHP in nondiabetic patients have revealed that Myofascial Release (MFR) to the calf muscles and plantar fascia is a practical manual therapy technique [16]. Recent studies indicate that the Structural Diagnosis and Management (SDM) approach—targeting calf muscles, plantar fascia, lower limb muscles, and myoneural structures—offers short‐ to intermediate‐term pain relief and improved functional independence in people with PHP. However, PHP is higher in DM cases and has a poor prognosis, and there is a significant research gap addressing effective manual therapy approaches for PHP in people with DM [17, 18, 19, 20, 21].

Therefore, the primary goal of this study is to compare the effectiveness of two manual therapy approaches, SDM and MFR, in treating individuals with PHP who have DM. The objectives are (1) to determine baseline compatibility of both groups in sociodemographic and clinical variables; (2) to measure between‐group and within‐group posttreatment outcomes in pain, ankle ROM, muscle strength, activity limitation, and disability; and (3) to compare the follow‐up outcomes of both groups. After 8 weeks of interventions, the SDM or MFR group is expected to show better improvement in PHP for people with DM.

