### Sample Size Calculation

2.2

The required sample size was calculated using G*Power software version 3.1.9.7 (University of Kiel, Kiel, Germany). Based on an effect size of 0.50, with a significance level (*α*) of 0.05 and statistical power of 0.80, a total of 72 participants were required for the study. To assume a potential 25% dropout rate, the final adjusted sample size was increased to 90 participants, with 45 allocated to each group [3].

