### Participant Recruitment and Screening

2.3

Between September 2025 and March 2026, DM with PHP were recruiting from three hospitals in Jashore, Bangladesh. Participants were screened for eligibility by two trained research assistants, and those who met the criteria provided written informed consent. Following CONSORT guidelines, participants were randomly assigned to their allocated groups using a concealed allocation method. Four blinded assessors conducted baseline assessments prior to the intervention's commencement. The intervention follows a standardized, concealed protocol, with participants blinded to group allocation to minimize bias.

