### Study Procedure

2.11

After screening by trained research assistants, eligible participants were thoroughly informed about the study's objectives and procedures, and then obtain their written informed consent. Once screened, participants were randomly assigned to their allocated groups using a predetermined randomization sequence to ensure unbiased allocation. Four blinded assessors collected baseline data at the study centre using an ethically approved questionnaire designed specifically for this research, which includes sociodemographic information and clinically relevant measures to confirm baseline compatibility with no statistically significant differences between groups. Following the baseline assessment, participants receive their assigned intervention for 8 weeks. After this period, blinded assessors will perform posttest (Week 8) and follow‐up (Week 20) evaluations by measuring primary and secondary outcome variables. This entire study procedure strictly following the SPIRIT 2013 guidelines (Table 1), ensuring methodological rigor and ethical compliance throughout the study.

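### The arms are compared with t-tests and change scores, and no analysis uses the baseline value as a covariate, so available precision is lost

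*Protocol article*

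**What the plan says.** Section 2.15 (Data Analysis) of the protocol article states the between-arm method: between-group and within-group "differences will be analyzed using independent and paired" t-tests, with Mann-Whitney U and Wilcoxon signed-rank tests for non-normal data. It also plans:

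- a repeated-measures ANOVA over baseline, week 8 and week 20, with the Friedman test as its nonparametric alternative;
- an evaluation of change scores;
- use of laterality in the analysis of ROM and muscle strength.

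VAS, ROM, strength and FFI are all scheduled at baseline (Table 1; section 2.7). No planned analysis is described as adjusting for the baseline value of the outcome.

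On comparability of the arms, section 2.15 says only that baseline characteristics will be reported. Section 2.11 (Study Procedure) goes further and says that baseline data serve "to confirm baseline compatibility with no statistically significant differences between groups". The Introduction makes it the first objective "to determine baseline compatibility of both groups in sociodemographic and clinical variables".

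**The concern.** The baseline value of an outcome usually predicts its later value. A comparison that conditions on it removes that part of the noise. A raw-score t-test leaves all of it in. A change score removes it with a fixed slope of 1 instead of the slope the data support. The trial already collects the baseline values, so the precision is available at no extra measurement cost.

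Two features add to this. First, raw scores and change scores are both planned and neither is named as decisive. The two can give different answers in the same data, and which is more powerful depends on r. Second, section 2.11 looks for reassurance in non-significant baseline differences. After randomisation, any baseline difference is due to chance. A non-significant test does not remove an imbalance in a prognostic variable; adjustment deals with it.

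What is at stake is power and a settled primary comparison in a trial that section 3 itself describes as limited in size.

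**Working it through.** **Inputs.** From section 2.2: "Based on an effect size of 0.50", a significance level "of 0.05 and statistical power of 0.80", and "a total of 72 participants were required for the study", raised to 90 (45 per arm). From section 2.15: "All statistical tests will be two‐tailed". Assumptions: the type of effect size is not named and is read as Cohen's d; r is not given and is varied from 0.3 to 0.8; the SD is taken as equal at baseline and week 8.

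**The plan's own figure.** For a two-sided t-test, n per arm = 2(1.960 + 0.842)²/0.50² = 62.8, so 63 per arm or 126 in total (64 and 128 by exact t). The stated 72 does not reproduce for this test. That is a separate matter, but it means there is no spare power to give away.

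**Variance of the treatment difference, relative to a raw-score t-test.**

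- Raw score: 1
- Change score: 2(1 − r)
- ANCOVA: 1 − r²

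ANCOVA against raw score is 1 − r², which is below 1 for any r above 0. ANCOVA against change score is (1 − r²)/[2(1 − r)] = (1 + r)/2, which is below 1 for any r below 1. So ANCOVA is the most precise of the three for every r strictly between 0 and 1. The change score is worse than the raw score below r = 0.5 and better above it.

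**Power.** The noncentrality is 0.50 × √(n/2)/√v, where v is the variance factor. With n = 45 and v = 1 it is 0.50 × √22.5 = 2.37, which gives 65.0% by the noncentral t. At r = 0.5, ANCOVA has v = 0.75, so 2.37/√0.75 = 2.74, which gives 77.3%. The other entries follow in the same way.

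| r | Raw, 45/arm | Change, 45/arm | ANCOVA, 45/arm | Raw, 36/arm | Change, 36/arm | ANCOVA, 36/arm |
|---|---|---|---|---|---|---|
| 0.3 | 65% | 51% | 69% | 55% | 42% | 59% |
| 0.5 | 65% | 65% | 77% | 55% | 55% | 68% |
| 0.6 | 65% | 75% | 83% | 55% | 65% | 74% |
| 0.7 | 65% | 86% | 91% | 55% | 77% | 83% |
| 0.8 | 65% | 96% | 97% | 55% | 91% | 94% |

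Total N for 80% power (normal approximation) at r = 0.3, 0.5, 0.6, 0.7 and 0.8 is 126 throughout for the raw score; 176, 126, 102, 76 and 52 for the change score; and 116, 96, 82, 66 and 46 for ANCOVA. With all 90 analysed, ANCOVA reaches 80% power at r of about 0.55.

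**Does the rest of section 2.15 supply the adjustment?** In the repeated-measures ANOVA, baseline is an outcome. The group-by-time contrast therefore compares changes, and the group main effect is diluted by a time point before treatment. The Friedman test has no between-arm factor, so with non-normal data Mann-Whitney U is the only arm comparison left. Laterality is confined to ROM and strength, so the primary VAS comparison remains unadjusted.

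**The case against.** The strongest reply is that the planned tests are sound. Under randomisation, raw-score and change-score comparisons are both unbiased, and a reader who infers that the analysis is biased or invalid goes too far. This stands: the loss is one of precision.

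A reader might also infer that baseline data play no part in the analysis. They do, as a time point in the repeated-measures ANOVA and in the change scores. The accurate statement is that baseline is never a covariate. Nor is every outcome wholly unadjusted, since laterality is promised for ROM and strength.

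It is tempting to read the plan as putting baseline significance tests in the place of adjustment. The documents do not say so. Section 2.15 lists no baseline test, and the support is one clause in section 2.11, which deserves a wording change and no more.

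The gain depends on an unknown r. At r = 0.8 the change-score test loses about one percentage point (96.0% against 97.4%), and from r = 0.7 it already exceeds 80% with 45 per arm. This stands too. But the plan does not make the change score decisive, and the raw-score test stays at 65% at those same values of r.

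Finally, patients are "recruiting from three hospitals in Jashore, Bangladesh", and one might conclude that a centre term is required. Section 2.5 does not describe randomisation stratified by hospital, so centre is an option and its absence is not a fault.

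Deferral to an unseen analysis plan is not an answer, because the article itself states the between-arm tests.

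**Conclusion.** The point holds as a matter of efficiency and specification. The article fixes between-arm tests that do not condition on baseline, leaves open whether raw or change scores decide, and so gives up precision that its own data could provide. With 45 per arm and no dropout, ANCOVA adds about 4 to 32 percentage points of power over the raw-score t-test (69 − 65 at r = 0.3; 97 − 65 at r = 0.8). Over the change-score test it adds about 18 points at r = 0.3 and about 1 at r = 0.8. These figures rest on 0.50 being Cohen's d, on equal SDs at baseline and week 8, and on an assumed r. The ordering of the three methods does not depend on which r between 0 and 1 is true. The baseline-comparability clause in section 2.11 is a lesser, linked fault. This should be changed, but it does not threaten the validity of the trial.

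**What to change.** In a dated amendment, made before any unblinded data are seen:

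1. Name one primary between-arm analysis: ANCOVA, or an equivalent mixed model, of week 8 VAS adjusted for baseline VAS.
2. Use the same model for week 20 VAS and for ROM, strength and FFI, each with its own baseline value. Keep laterality for ROM and strength.
3. Add centre (three levels) as a covariate if wished; it is optional.
4. Report the adjusted mean difference with its 95% CI.
5. In section 2.11, remove the criterion of no significant differences between groups, and describe the arms at baseline by summary statistics only.

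No new data are needed, since every covariate is already scheduled. The cost is the amendment itself. Section 4 says that recruitment is under way, and section 2.14 sends protocol changes to the Ethical Review Board and gives the monitors interim access to data. The amendment should therefore be dated and should record that it preceded any unblinded look.

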### Eligibility Criteria

2.4

Participants were screened for eligibility by trained research assistants. Inclusion criteria: (1) age between 30 and 65 years for both male and female [17]; (2) participants diagnosed with unilateral or bilateral heel pain or plantar fasciitis (according to ICD‐10 criteria, ICD diagnosis codes M72.2); (3) localized pain in the plantar region of the foot when placed their barefoot on the floor in the morning; (4) ankle dorsiflexion is more limited than plantar‐flexion; and (5) suffering with PHP from more than 4 weeks [17]. Exclusion criteria: (1) confirmation and diagnosis of diabetic peripheral neuropathy; (2) history of lower extremity fracture, rheumatoid arthritis, osteoarthritis, carcinoma, surgery of the foot, and metal implant around ankle [15]; (3) active foot ulceration, infection, severe peripheral vascular disease, gangrene of the foot, cyanotic symptom, and severe neurological condition [11]; (4) contraindicated to manual therapy or exercise intervention [17]; and (5) participants taken corticosteroids injection within 6 months [16].

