#### Range of Motion (ROM)

2.10.1

Participants actively perform dorsiflexion and plantarflexion using a digital dynamometer (ActiveForce‐2), with measurements recorded in degrees via the device's app. A study reported excellent reliability for the portable dynamometer, with ICC values of 0.972 for dorsiflexion and plantarflexion. Additionally, strong reliability was found between right and left ankle measurements: plantarflexion ICC = 0.89 and dorsiflexion ICC = 0.94 [24, 25].

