#### Muscle Strength

2.10.2

A portable digital hand dynamometer (ActiveForce‐2) and its companion app is used to assess isometric strength of the dorsiflexors and plantarflexors of the affected foot, with measurements recorded in kilogram‐force (kgf). Previous research has demonstrated that portable dynamometers exhibit high inter‐rater and test–retest reliability, with strong correlations for dorsiflexion and plantarflexion strength (*r* = 0.827, *r* = 0.973) [25].

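### Laterality is promised in the ROM and strength analyses, but the between-group tests named cannot hold it, and the foot to be measured in bilateral participants is not fixed

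*Protocol article*

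**What the plan says.** Eligibility Criteria (2.4) admits "participants diagnosed with unilateral or bilateral heel pain or plantar fasciitis", so a participant may have two painful feet.

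Muscle Strength (2.10.2) uses a hand dynamometer "to assess isometric strength of the dorsiflexors and plantarflexors of the affected foot". The wording is singular, with no rule for a participant in whom both feet are affected. Range of Motion (2.10.1) says "Participants actively perform dorsiflexion and plantarflexion using a digital dynamometer" and does not say which ankle. The same section reports that "strong reliability was found between right and left ankle measurements", with ICCs of 0.89 for plantarflexion and 0.94 for dorsiflexion.

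Data Analysis (2.15) states that laterality "will be recorded and incorporated into the analysis to minimize potential confounding effects on ROM and muscle strength outcomes". Between- and within-group "differences will be analyzed using independent and paired" t-tests, or by Mann-Whitney U and Wilcoxon signed-rank tests if the data are not normal. For comparisons across the three time points, repeated-measures "ANOVA will be applied for normally distributed data, with the Friedman test used as the nonparametric alternative".

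**The concern.** Two things do not fit together.

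First, section 2.15 makes a promise and also names the tools, and the tools for the treatment comparison cannot keep the promise. A t-test or a Mann-Whitney test compares two sets of values and has no place for a third variable.

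Second, the measured quantity is not fixed for bilateral participants. If the foot is left to the assessor or analyst, it could be chosen late or differ between visits, and a change score could then compare two different feet. If both feet were measured and entered as separate observations, the two rows from one person would be strongly correlated and the confidence intervals too narrow.

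Between-group ROM and strength differences are a stated objective in the Introduction, so these are results the trial intends to report.

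**Working it through.** The plan gives no figure of its own on this point, so there is nothing to reproduce. The check has three parts.

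**1. Which named methods can hold laterality?**

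| Method in 2.15 | Use given to it | Can hold laterality? |
|---|---|---|
| Independent t-test | between groups | no |
| Mann-Whitney U | between groups | no |
| Paired t-test | within group | no |
| Wilcoxon signed-rank | within group | no |
| Friedman | three time points | no |
| Repeated-measures ANOVA | three time points | yes, as a between-subject factor |

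Five of six cannot, and both tests assigned to the group comparison are among the five.

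**2. How far could laterality confound?** Allocation is random, so imbalance arises only by chance. With 45 per arm and bilateral share b, the SD of the between-arm difference in that share is √(2b(1−b)/45):

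- b = 0.2: √(0.32/45) = 0.084
- b = 0.3: √(0.42/45) = 0.097
- b = 0.5: √(0.50/45) = 0.105

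An imbalance of 8 to 11 percentage points is thus ordinary. Adjustment is reasonable, but no systematic bias is implied.

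**3. What if both feet became independent rows?** The article does not say this will be done; the calculation only bounds the harm. Inputs:

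- the bilateral share b is not stated and is assumed to be 10% to 50%;
- the right-left correlation r is taken as 0.89 to 0.94 from section 2.10.1, with 0.5 as an assumed lower value;
- nominal two-sided α is 0.05.

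The variance inflation is

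VIF = [(1−b) + b(2+2r)]/(1+b) = 1 + 2br/(1+b),

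and the true type I error is 2[1 − Φ(1.96/√VIF)]. For example, b = 0.2 and r = 0.89 give VIF = 1 + 0.356/1.2 = 1.297 and an error of 0.0852.

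| b | r = 0.50 | r = 0.89 | r = 0.94 |
|---|---|---|---|
| 10% | 0.0606 | 0.0690 | 0.0701 |
| 20% | 0.0696 | 0.0852 | 0.0872 |
| 30% | 0.0773 | 0.0989 | 0.1017 |
| 50% | 0.0896 | 0.1205 | 0.1244 |

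A simulation with 45 persons per arm, r = 0.9 and 20,000 runs per cell gave 0.084, 0.102 and 0.124 at 20%, 30% and 50% bilateral, in agreement with the formula.

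A unilateral/bilateral term would not remove this inflation, because it does not model the correlation between two feet of one person. With one value per participant the inflation does not arise.

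**The case against.** The strongest reply is that the article identifies laterality, records it and commits to using it, and that how it enters the model and which foot is indexed are details for a fuller plan. On the index foot alone this is close to right. It does not dispose of the point, because the article goes on to name the tests, and those named for the group comparison do not carry out the commitment.

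A second reply is that repeated-measures ANOVA can take laterality, and that the t-test or Mann-Whitney test could be run within laterality strata. Both are possible. But the ANOVA is assigned to the time comparison, and stratified tests are not mentioned. Stratified tests would also give two separate results instead of one adjusted estimate; at an assumed 20% bilateral share, the bilateral stratum would hold 0.2 × 45 = 9 persons per arm.

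Third, a reader might infer that an analyst is bound either to enter both feet as rows or to pick a foot visit by visit, so that the result must be wrong. The document does not support this. Participants are randomised, data are coded by one ID per participant, and section 2.8 lists the affected foot among the baseline variables. The participant is the apparent unit; one fixed foot or a person-level mean would fit the text and would not inflate the error.

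Fourth, a reader might extend the point to the primary outcome. Section 2.9.1 describes a single 10 cm VAS rating and no scoring by foot, and one rating per person raises no clustering problem. The flaw is not shown there.

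**Conclusion.** The point holds for the secondary ROM and strength outcomes. The adjustment promised in section 2.15 cannot be made with the tests assigned to between-group differences, and the measured foot is undefined for an eligible class of participants.

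The certain loss is modest: the stated control of laterality is absent from the treatment comparison, and the choice of foot is left open. The type I error of about 7-12% (about 6-9% at r = 0.5) is conditional. It requires feet to be analysed as independent rows, rests on an assumed bilateral share of 10-50%, and borrows ICCs that the article cites as reliability figures as a stand-in for the correlation between feet in this population. It should not be read as the expected error rate of the trial. The change is worth making because it is cheap and delivers what the article already promises.

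**What to change.** For ROM and strength, replace the independent t-test or Mann-Whitney comparison with a linear model (ANCOVA) of the Week 8 value, and likewise of the Week 20 value, on arm, baseline value and laterality (unilateral or bilateral). Report the adjusted mean difference with its 95% confidence interval.

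Use one value per participant, from an index foot fixed at baseline by a written rule and kept at all three visits, and name that foot in sections 2.10.1 and 2.10.2. If both feet are measured and kept, use a mixed model with a participant random effect.

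Cost: the model needs no new variable, since laterality and baseline values are already to be recorded. The second foot of bilateral participants is unused in the main analysis. A rule that picks the more painful foot would need foot-level baseline pain, which the article does not say is recorded. As recruitment is under way, the sponsor should check which feet have been measured so far and choose a rule that those data can support, before any comparison by arm.

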### Randomization and Blinding

2.5

Eligible participants with written informed consent were randomly allocated to their respective groups, either the SDM or the MFR group. The randomization sequencing process was conducted using the “Rand” function in Microsoft Excel 2013 software. A sequential list of participants' IDs, sorted according to the randomly generated numbers. This procedure helps to prevent bias. Participants were allocated to a parallel intervention group in a 1:1 ratio. This is an assessor‐ and participant‐blinded randomized clinical trial, with outcome assessors and participants blinded to group allocation. Physiotherapists delivering manual therapy could not be blinded, but both groups received identical conventional physiotherapy to control for nonspecific effects. Therapists were trained to follow standardized protocols and avoid discussing treatment or outcomes with participants or assessors to minimize bias. Inter‐rater reliability for manual techniques will be established, and any unblinding will be documented and reported.

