### Outcome Measurements

2.7

Baseline sociodemographic and clinical characteristics were collected immediately after obtaining informed consent from participants and before the initiation of the intervention. All primary and secondary outcomes were planned to analyze at three time points: baseline (Week 0), posttest (Week 8), and follow‐up (Week 20), by four trained and blinded assessors.

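### LOCF is fixed as the only intention-to-treat method; it can bias the SDM–MFR contrast when loss differs between arms in amount or timing, and it dilutes a true difference when loss is early

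*Protocol article*

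**What the plan says.** The Data Analysis section (2.15) of the protocol article states that an intention-to-treat "analysis using the last observation carried forward method will be applied to handle missing data and preserve the validity of the analysis". No other missing-data method and no sensitivity analysis is named. The same section plans repeated-measures ANOVA across the three visits, t-tests or rank tests between and within groups, and an evaluation of change scores.

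The Sample Size Calculation section (2.2) sets the scale of the expected loss: "To assume a potential 25% dropout rate, the final adjusted sample size was increased to 90 participants, with 45 allocated to each group". The Outcome Measurements section (2.7) and Table 1 give three assessments, at Weeks 0, 8 and 20, so there are only two post-baseline values per participant. The Results paragraph of the Abstract says that the trial is meant to examine both immediate and sustained effects.

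**The concern.** With so few visits, what is carried forward matters a great deal.

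- **Loss before Week 8.** The only value available is the untreated baseline. It is used at Week 8 and again at Week 20, so the participant's change score is exactly zero. Both arms receive active manual therapy plus the same conventional physiotherapy, so improvement is expected in both, and a zero change is a poor guess in either arm.
- **Loss after Week 8.** The Week 8 value stands in for Week 20. That presumes the answer to the durability question, which the Week 20 visit is there to settle.

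If early loss differs between arms, the arm with more loss looks worse for that reason alone. If early loss is equal and one treatment really is better, the difference shrinks. The rule governs the primary VAS comparison and every secondary outcome. It is a positive choice with a stated justification, so it is not a detail left for a later plan to supply.

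**Working it through.** **Inputs from the protocol article.** Randomisation is 1:1 with 45 per arm, tests are two-sided at 0.05, assessments are at Weeks 0, 8 and 20, the primary outcome is a 10 cm VAS, and the dropout allowance is 25%.

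**The plan's own dropout figure.** 72 × 1.25 = 90 reproduces the stated total. Read as a loss rate, 1 − 72/90 = 20%, so 90 enrolled leaves 72 completers only if loss is 20%. At 25% loss, 90 × 0.75 = 67.5 remain. The plan gives no figure for the effect of LOCF, so there is nothing further to reproduce.

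**Assumptions not in the documents.** Mean VAS 6.5 at baseline and 3.0 at Week 8, stable to Week 20 (a fall of 3.5 cm). SD 2 cm at each visit, within-person correlation 0.5. Loss is unrelated to outcome within each arm.

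**Formulas.** Let p be the proportion of an arm lost before Week 8 and f the mean fall in that arm. The LOCF-completed arm is a mixture of baseline and treated values:

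- mean = 6.5 − f(1 − p)
- variance = 2² + p(1 − p)f²
- standard error of the contrast = √[(variance A + variance B)/45]
- with no true difference, bias = (p_A − p_B) × f
- rejection rate ≈ Φ(z − 1.96) + Φ(−z − 1.96), where z = |mean contrast| / standard error

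Loss after Week 8 does not enter p when scores are stable, because the carried Week 8 value then has the same mean and SD as the missing Week 20 value.

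**No true difference, 30% v 20% loss.**

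- All early: bias 0.10 × 3.5 = 0.35 cm. Variances are 4 + 0.21 × 12.25 = 6.57 and 4 + 0.16 × 12.25 = 5.96. SE = √(12.53/45) = 0.528 and z = 0.66, so type I error is about 10%.
- Half late (15% v 10% early): bias 0.05 × 3.5 = 0.175 cm (0.17 in simulation). Variances are 5.56 and 5.10, SE = 0.487 and z = 0.36, so type I error is about 6%.
- All late, stable scores: bias 0 cm and type I error 5%.

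**True difference 1.0 cm (falls of 4.5 and 3.5 cm), 25% loss in both arms.**

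- All early: estimate 0.75 × 1.0 = 0.75 cm. Variances are 4 + 0.1875 × 20.25 = 7.80 and 4 + 0.1875 × 12.25 = 6.30. SE = 0.560 and z = 1.34, so power is about 27%.
- Half late: estimate 0.875 × 1.0 = 0.875 cm (0.88). SE = 0.507 and z = 1.73, so power is about 40%.
- All late, stable scores: estimate 1.0 cm. SE = 2√(2/45) = 0.422 and z = 2.37, so power is about 65%.
- Observed values only, 33.75 per arm: SE = 2√(2/33.75) = 0.487 and z = 2.05, so power is about 53% with an unbiased 1.0 cm.

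Simulation of the t-test on LOCF-completed data agrees with these figures.

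**Range over other assumptions.**

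| Scenario (no true difference) | Fall | Spurious difference | Type I error |
|---|---|---|---|
| 25% v 25%, all early | 3.5 cm | 0.00 cm | 5% |
| 30% v 20%, all early | 3.0 cm | 0.30 cm | 9% |
| 35% v 15%, all early | 3.0 cm | 0.60 cm | about 22% |
| 35% v 15%, all early | 3.5 cm | 0.70 cm | about 26% |
| 25% in each arm, one all early, the other all late | 3.0 cm | 0.75 cm | about 35% |

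The last row shows that equal totals do not protect the contrast if the timing differs. With a 3.0 cm fall in the comparator arm, the early-loss power for a true 1.0 cm is 29%, so the range for that case is 26–29%.

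**The case against.** A reader might infer that LOCF biases the contrast and inflates the false-positive rate whatever happens. The documents do not support that. With loss equal in amount and timing and no true difference, LOCF gives no bias and keeps 5%. Inflation needs loss that differs between arms, and nothing in the protocol predicts it: both arms have the same session schedule and the same conventional physiotherapy, and participants are blinded. The article gives one overall allowance, which it calls potential. The unequal splits above are assumptions.

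The early-loss figures are also the unfavourable end. With 12 weeks of follow-up after treatment, much of the loss may come after Week 8. If scores are then stable, LOCF is unbiased and loses no power. Whether scores are stable is unknown, so a Week 8 value carried to Week 20 cannot be called wrong in advance; it can only be called untested.

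Nor are observed data a cure. They are unbiased here because loss was assumed unrelated to outcome. When non-responders were made likelier to leave (30% v 20%, no true difference), observed data at Week 8 gave −0.25 cm and 7.4% type I error, against 0.28 cm and 7.6% for LOCF. Finally, an analysis plan that is not shown might add sensitivity analyses.

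All of this limits the size of the problem and makes it conditional. It does not rescue the rule. The protocol names LOCF alone and asserts that it protects validity, yet the method is safe only under patterns of loss that the trial cannot guarantee.

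**Conclusion.** The point holds in conditional form. LOCF as the sole intention-to-treat method is a poor stated rule for a trial with two post-baseline visits and an allowance of 25% dropout. The stated reason for choosing it is not correct in general.

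With 30% v 20% loss and no true difference, the harm runs from nothing (all loss late, scores stable) through 0.17 cm and 6% (half late) to 0.35 cm and 10% (all early). With a true 1.0 cm difference and 25% loss in both arms, the estimate runs from 1.0 cm with no loss of power (all late, stable) through 0.88 cm and 40% power to about 0.75 cm and 26–29% power (all early). Greater imbalance, or timing that differs between arms, makes it worse.

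These sizes rest on the assumed SD, fall in pain, dropout split and loss unrelated to outcome, none of which the protocol gives. The direction does not depend on their exact values, provided pain falls during treatment and some participants are lost before Week 8.

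**What to change.** Before any outcome data are analysed, replace LOCF as the primary method with a likelihood-based linear mixed model (MIXED in SPSS, REML, unstructured covariance). Put the Weeks 0, 8 and 20 VAS values all in the outcome vector, with visit and arm-by-visit effects and baseline means constrained equal between arms. Every randomised participant with a baseline value is then included. A model that uses baseline only as a covariate would drop anyone lost before Week 8, so it could not be described as analysing all randomised participants. Multiple imputation by arm under missing at random is an acceptable alternative.

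Delete the statement that LOCF preserves validity. Keep LOCF at most as a sensitivity analysis, and add a delta-adjusted multiple imputation to cover loss related to outcome, which the mixed model under missing at random does not fully address.

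The cost is a wording change and slightly more analysis work, in software the protocol already names. No extra participants, visits or data are needed, and the article says that the trial is still recruiting.
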